# Protocol for a randomised controlled feasibility study examining the efficacy of brief cognitive therapy for the treatment of panic disorder in adolescents (PANDA)

**DOI:** 10.1186/s40814-022-01009-z

**Published:** 2022-03-03

**Keywords:** Panic disorder, Adolescent, Young people, Youth, Cognitive therapy, CBT, Psychological treatment, Brief

## Abstract

**Background:**

Panic disorder occurs in between 1 and 3% of adolescents, is associated with high levels of co-morbidity, and without treatment, appears to have a chronic course. To improve access to effective psychological interventions, briefer versions of cognitive behaviour therapy (CBT) have been developed and evaluated for preadolescent children with anxiety disorders. However, there are currently no brief evidence-based CBT interventions for adolescents with anxiety disorders that can be delivered in less than eight sessions. Given that a brief version of cognitive therapy has been shown to be effective in adults with panic disorder, it is possible that an adapted version could be effective for adolescents with panic disorder.

**Methods:**

The study will examine whether a definitive trial can be conducted, based on a single-centre feasibility randomised controlled trial using several well-defined criteria. Between 30 and 48 young people (age 11–18 years) who meet diagnostic criteria for panic disorder, attending a routine clinical service will be randomly allocated to receive either (i) brief cognitive therapy or (ii) a general form of CBT treatment that is more commonly used for adolescents with anxiety disorders. Both will be delivered 1:1 by a therapist and involve five treatment sessions and two booster sessions. Young people’s outcomes will be assessed at the end of treatment and at 3-month follow-up, and qualitative interviews will be conducted to examine acceptability. We will also explore outcomes 1 year after the completion of treatment.

**Discussion:**

This study will test the feasibility of a randomised controlled trial to compare brief cognitive therapy to a general form of CBT for adolescents with panic disorder in the UK. The outputs from the study will provide a clear indication of the feasibility of a future definitive trial and, if indicated, the critical resources that will be required and key information to inform the design and maximise the successful completion of the trial. This has the potential to bring direct benefits to young people and their families, as well as services and society more broadly.

**Trial registration:**

This trial is registered on the ISRCTN Registry, registration number ISRCTN14884288, registered retrospectively on 05/12/2019.

**Supplementary Information:**

The online version contains supplementary material available at 10.1186/s40814-022-01009-z.

## Introduction

For many people, panic disorder begins in adolescence [1], with between 1 and 3% of adolescents aged 11–19 years meeting diagnostic criteria for panic disorder [2, 3]. This early onset may be associated with more severe symptoms and a worse outcome than panic disorder that starts in adulthood [4]. Young people with panic disorder commonly avoid a range of environments, including school cafeterias or restaurants, small rooms and auditoriums [5], which is likely to have a significant impact on functioning at school and with friends. Furthermore, panic disorder in adolescence has high rates of comorbidity, including other anxiety disorders and depression, and is associated with the subsequent onset and persistence of alcohol abuse and dependence [5–7]. If left untreated, it appears to have a chronic course [6]. These factors highlight the need for effective and accessible treatments.

Two psychological treatments have been extensively evaluated with adults with panic disorder and shown to be similarly effective in their original format (i.e. 12 to 15 sessions): panic control treatment (PCT) [8] and cognitive therapy (CT) for panic disorder [9]. Both treatments have been shown to be superior to a range of other treatments including relaxation therapy, supportive psychotherapy and medication [10]. However, when briefer forms of the two treatments were developed and evaluated, only the brief form of CT remained as effective as the full treatment [9, 11]. Specifically, a version of CT involving self-study modules and 5 sessions (plus two booster sessions) of therapy (B-CT) did not differ significantly from the full 12 session (plus two booster sessions) treatments (F-CT) immediately or at 12-month follow-up (panic-free at post-treatment: F-CT 79%, B-CT 71%; 12-month follow-up: F-CT 71%, B-CT 79%). No participants dropped out of treatment, and there were large effect sizes for both the full and brief treatments on a measure of panic symptoms from pre- to post-treatment and pre- to 12-month follow-up (post-treatment: F-CT *d* = 2.9, B-CT *d* = 2.9; 12-month follow-up: F-CT *d* = 2.8, B-CT *d* = 3.2). Both treatments were also significantly more effective than a waitlist control in reducing panic symptoms on a range of measures (*d* ranged from 1.35 to 2.98).

In contrast to treatment for adults, the treatment of panic disorder in adolescents has been largely neglected, and a considerable number of randomised controlled trials treating anxiety in children and adolescents have excluded young people who have panic disorder as the primary problem [12–14]. The most substantial evidence base for CBT for a broad range of anxiety disorders in children and adolescents comes from trials using a general, transdiagnostic treatment approach (e.g. the ‘Coping Cat’ treatment protocol [15] or the adolescent version, the ‘C.A.T. Project’ [16]). The treatment involves anxiety management (e.g. psychoeducation, cognitive restructuring and relaxation techniques) prior to graded exposure, where the young person learns to face their fears through exposure to the feared situation or stimulus in a graded way. Meta-analyses have demonstrated that around 50% of children and adolescents are free of their primary diagnosis at the end of CBT [17]. However, outcomes for young people with panic disorder specifically are unknown. In the UK, CBT appears to be the most used treatment approach by clinicians in routine clinical practice to treat young people with panic disorder. However, a recent national survey of over 400 clinicians working in Child and Adolescent Mental Health Services (CAMHS) in the National Health Service (NHS) found that only 2.6% was able to identify any specific treatment protocols to treat young people with panic disorder, either within transdiagnostic or disorder-specific treatments [18].

Currently, young people face significant difficulties to access evidence-based treatments. Fewer than one in five adolescents in need of treatment receive appropriate psychological interventions [19], and many face significant delays or spend months on waiting lists for treatment within routine clinical services [20]. In order to improve access to effective psychological interventions, briefer versions of CBT have been developed that can be delivered by non-specialists, so that more intensive treatments can be reserved for those who do not, or who are unlikely to, benefit from a brief treatment [21]. Brief CBT has recently been defined as referring to either low intensity CBT (i.e. 6 h or less of contact time with a therapist, using self-help materials) and/or brief high intensity CBT (i.e. based on the standard evidence-based CBT treatment, with therapy contact time 50% or less than the full CBT intervention) [22]. Suitable brief CBT treatments have been developed and evaluated for preadolescent children [23]; however, there has been limited research attention on brief CBT interventions for adolescents with anxiety disorders. Of the sixteen studies of psychological therapies for adolescents with anxiety disorders (including panic disorder) identified in a recent meta-analysis [24], only one study [25], involving adolescents with a range of anxiety disorders, fulfilled the definition of brief CBT.

Many treatments for anxiety disorders in children and adolescents have successfully been adapted from treatments shown to be effective in adults. Although Barlow and Craske’s PCT has been successfully adapted for adolescents with panic disorder in the USA (PCT-A) [26], the two derivations of treatment require a considerable amount of therapist time (between 11 and 22 h of therapy) [27, 28]. In addition, the intensive form of treatment, which has the most empirical support, would be difficult to implement in NHS CAMHS settings as it requires treatment to be conducted by a therapist for several hours over consecutive days. To date, there has been no adaptation of Clark’s cognitive therapy for adolescents with panic disorder, despite emerging evidence that the psychological processes targeted in CT for adults may also be evident in adolescents [29–31]. Given that the brief version of this treatment has been shown to be effective in adults with panic disorder, with a large effect size, it is possible that recovery rates for adolescents could be substantially improved, and treatment considerably shortened by using this alternative treatment approach, adapted for use with adolescents.

To maximise the likelihood of a future successful large-scale randomised controlled trial (RCT), the aim of this study is to test the feasibility of a RCT to compare brief cognitive therapy for panic disorder (adapted for adolescents) to a general form of CBT treatment that is more commonly used for adolescents with anxiety disorders, including panic disorder, in the UK.

## Method

### Aims of the study

The specific aims of this study are as follows:Identify appropriate clinical outcome and economic measures for a subsequent definitive trial.Explore the acceptability of the treatments and trial procedures.Establish likely recruitment rates.Establish the likely rate of treatment drop-out.Establish likely retention to research assessments post treatment and at 3-month follow-up.Explore retention to a brief 12-month follow-up.Establish if brief cognitive therapy can be delivered so that it is clearly distinct from a general form of CBT, with high levels of fidelity by practitioners and credibility with patients in both arms.Conduct exploratory analyses of possible outcomes for the two treatments including changes in anxiety symptoms, diagnostic status, quality of life, healthcare resource use and other outcomes identified through patient and public involvement and engagement (PPIE).Describe negative impacts of the treatments and the trial procedures (to patients, their parents and clinicians).Explore young people’s outcomes on measures of symptom and functional impairment.

The outputs from the study will provide a clear indication of the feasibility of a future definitive trial and, if indicated, the critical resources that will be required and key information to inform the design and maximise the successful completion of the trial. Information about how and when each aim will be measured, and the criteria required to be met to warrant progression to a full trial, can be found in Table 1. Progression criteria were developed based on recent similar studies (e.g. [32]) and in consultation with PPIE representatives, clinicians and researchers. Recruitment, retention, distinctness of treatment and fidelity of treatment delivery will be evaluated and determined as meeting one of three success levels using the following traffic light system:Green indicates that progression to a definitive trial is possible without needing to substantially change design or delivery.Amber indicates a need for more resources and/or new ideas for recruiting and retaining participants, ensuring that treatments are distinct and delivered with high levels of fidelity.Red indicates that a definitive trial may not be viable.

**Table 1 Tab1:** Aims, outcome measures and progression criteria

	Aims	Measure	Timepoint	Progression criteria
a.	Identify appropriate clinical outcome and economic measures for a subsequent definitive trial	Clinical outcomes: ADIS-C/P/KSADS-C/P (or DAWBA and ADIS-panic section) (diagnosis and CSR)	Routine assessment/pre-randomisation	Appropriate measures identified
		Clinical outcomes: PDSS-A, RCADS-C/P, CAIS-C/P Health economic measures: CSRI, EQ-5D, CHU-9D	Enrolment/pre-treatment	
		Clinical outcomes: PDSS-A, RCADS-C/P, CAIS-C/P Health economic measures: CSRI, EQ-5D, CHU-9D	Post-treatment	
		Clinical outcomes: ADIS-C/P/KSADS-C/P (or DAWBA & ADIS-panic section) (diagnosis and CSR), CGI-I, PDSS-A, RCADS-C/P, CAIS-C/P Health economic measures: CSRI, EQ-5D, CHU-9D	3-month follow-up	
b.	Explore the acceptability of the treatments and trial procedures	Credibility and expectation of improvement scale-C/P	Enrolment	No serious concerns raised
		ESQ-C/P	Post-treatment and 3-month follow-up	No serious concerns raised
		Qualitative interview (young people, parent/carers, clinicians)	Post-treatment/3-month follow-up	No serious concerns raised
c.	Establish likely recruitment rates	Screening logs maintained by site *n* = Approached *n*= Accepting *n* = Declining Reasons (coded) for decline of study invitation	At study entry and ongoing through study	Green: ≥ 30 participants recruited; ≥ 80% eligible participants agree to randomisation
				Amber: 20–29 participants recruited; 70–79% eligible participants agree to randomisation
				Red: < 20 young people are recruited; < 70% eligible participants agree to randomisation
d.	Establish the likely rate of treatment drop-out	Number withdrawing from treatment	Ongoing through study	Green: Treatment drop-out rate of ≤ 20% in both treatment arms
				Amber: Treatment drop-out rate of 21–30% in both treatment arms
				Red: Treatment drop-out rate of > 30% in both treatment arms
e.	Establish likely retention to research assessments post-treatment and at 3-month follow-up	Number of completed assessments - PDSS-A - All other clinical and health economic outcome measures	Ongoing through study	Green: ≥ 80% of participants will complete the PDSS-A at post-treatment and 3-month follow-up assessment
				Amber: 70–79% of participants complete the PDSS-A at post-treatment and 3-month follow-up assessment
				Red: < 70% of participants complete the PDSS-A at post-treatment and 3-month follow-up assessment
f.	Explore retention to a brief 12-month follow-up	Clinical outcomes: PDSS-A	12-months follow-up	No set criteria
g.	Establish if brief cognitive therapy can be delivered so that it is clearly distinct from a general form of CBT, with high levels of fidelity by practitioners in both arms	Therapy contents checklist	Each clinical session	Green: In both arms, sessions contain ≥ 80% ‘allowable’ features of the specific intervention
				Amber: In both arms, sessions contain 70–79% ‘allowable’ features of the specific intervention
				Red: In both arms, sessions contain < 70% ‘allowable’ features of the specific intervention
h.	Conduct exploratory analyses of possible outcomes for the two treatments including changes in anxiety symptoms, diagnostic status, quality of life and healthcare resource use	Clinical outcomes: PDSS-A, RCADS-C/P, CAIS-C/P Health economic measures: CSRI, EQ-5D, CHU-9D	Post-treatment	Not applicable
		Clinical outcomes: ADIS-C/P/KSADS-C/P (diagnosis and CSR), CGI-I, PDSS-A, RCADS-C/P, CAIS-C/P Health economic measures: CSRI, EQ-5D, CHU-9D	3-month follow-up	Not applicable
		Clinical outcomes: PDSS-A	12-months follow-up	Not applicable
i.	Describe negative impacts of the treatments and the trial procedures (to young people, their parents/carers and clinicians)	Adverse events	Ongoing through study	Serious negative impacts do not occur because of participation in the trial
		Qualitative interview (young people, parent/carers, clinicians)	Post-treatment/3-month follow-up	No serious impacts raised
j.	Explore young people’s outcomes on measures of symptom and functional impairment	Symptom measures: PDSS-A, RCADS-C/P, CAIS-C/P Functional impairment: ORS	Post-treatment	Not applicable
		Symptom measures: PDSS-A, RCADS-C/P, CAIS-C/P Functional impairment: ORS	3-month follow-up	Not applicable
		Clinical outcomes: PDSS-A	12-month follow-up	Not applicable

To feel confident that a definitive trial can be delivered without major study redesign, all progression criteria would need to be met (i.e. no serious concerns raised) or met within reasonable limits (i.e. within the green or amber traffic light domains).

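### Table 1 rows d and g attach the both-arms condition to every colour, so any result with the arms in different bands has no colour and one failing arm cannot make the row Red

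*Protocol article*

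**What the plan says.** In the protocol article, Method, Aims of the study, Table 1, row d sets three levels for treatment drop-out. The best level reads "Green: Treatment drop-out rate of ≤ 20% in both treatment arms". The middle level moves the band to 21–30% and keeps the condition that each of the two arms lies in it. The worst level does the same above 30%: "Red: Treatment drop-out rate of > 30% in both treatment arms".

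Row g, on distinctness and fidelity, uses the same construction with limits of 80% and 70%. Its lowest level begins "Red: In both arms, sessions contain < 70" (per cent).

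The text before the table says that the traffic-light criteria "will be evaluated and determined as meeting one of three success levels". It names recruitment, retention, distinctness and fidelity. Treatment drop-out is not in that list, but row d grades it with the same three colours. The same text adds: "Red indicates that a definitive trial may not be viable".

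The rule after the table is that "all progression criteria would need to be met", or "met within reasonable limits (i.e. within the green or amber traffic light domains". No text says how to grade a row when the arms fall in different bands.

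**The concern.** Requiring both arms is right for Green, where neither arm may fail. Repeated in Red it works the other way: a row is Red only if both arms fail together. A result of 0/15 drop-outs in one arm and 15/15 in the other is not Green, Amber or Red.

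A feasibility comparison of two therapies needs to detect that one of them is unacceptable or cannot be delivered as intended. Row d is the only numerical criterion for treatment drop-out, and row g the only one for session content. Neither can signal Red for a single arm. The purpose of pre-set progression criteria is to fix the decision before the data are seen, and these two rows do not do so for mixed results.

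**Working it through.** The document states no probability for these criteria, so there is no figure of the plan to reproduce. The check is first logical, then an exact binomial calculation.

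**Inputs.** The bands are those of row d. The sample size is 30 to 48 (Sample size) with 1:1 allocation (Randomisation), so about 15 to 24 per arm. True drop-out rates are assumptions shown as a range, and the arms are taken as independent.

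**Band combinations.** Two arms and three bands give 3 × 3 = 9 combinations. Only the 3 with both arms in the same band have a colour. The other 6 have none, and they include every case in which exactly one arm exceeds 30%.

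**Counts, rates rounded to whole per cent.**

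- 15 per arm: Green 0–3, Amber 4, Red 5–15 drop-outs. Coloured pairs: 4² + 1² + 11² = 138 of 16² = 256, so 118 (46%) have no colour.
- 24 per arm: Green 0–4, Amber 5–7, Red 8–24. Coloured pairs: 5² + 3² + 17² = 323 of 25² = 625, so 302 (48%) have no colour.
- Unrounded, 5/24 = 20.8% lies between the Green and Amber limits, and the second figure becomes 307 (49%).

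**Formulas.** Let G, A and R be the binomial probabilities that an arm falls in each band.

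- P(no colour) = 1 − (G₁G₂ + A₁A₂ + R₁R₂)
- P(Red as written) = R₁R₂
- P(Red if the worse arm decides) = 1 − (1 − R₁)(1 − R₂)

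**Example, 25% in both arms.**

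- 15 per arm: G = 0.4613, A = 0.2252, R = 0.3135. P(no colour) = 1 − (0.2128 + 0.0507 + 0.0983) = 0.638.
- 24 per arm, rounded: G = 0.2466, A = 0.5196, R = 0.2338. P(no colour) = 1 − (0.0608 + 0.2699 + 0.0547) = 0.615 (0.6146 before rounding). Unrounded, part of the Amber probability falls in the gap and the result is 0.766.

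**Example, 10% versus 40%, 15 per arm.** The bands are 0.9444, 0.0428, 0.0127 and 0.0905, 0.1268, 0.7827. P(no colour) = 1 − (0.0855 + 0.0054 + 0.0100) = 0.899.

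**Results, 15 / 24 per arm, whole-percent rounding.**

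| True drop-out | No colour, as written | Red, as written | Red, worse arm decides |
|---|---|---|---|
| 5% and 5% | 1% / 1% | <0.1% / <0.1% | 0.1% / <0.1% |
| 10% and 10% | 11% / 16% | <0.1% / <0.1% | 2.5% / 0.3% |
| 20% and 20% | 52% / 58% | 2.7% / 0.8% | 30% / 17% |
| 25% and 25% | 64% / 61% | 9.8% / 5.5% | 53% / 41% |
| 10% and 40% | 90% / 97% | 1.0% / 0.1% | 79% / 81% |

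The last column uses the product formula, for example 1 − (1 − 0.3135)² = 0.529. At these two arm sizes rounding does not change either Red column. Row g has the same logical gap. No probabilities are given for it because the document offers no basis for a distribution of checklist scores.

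**The case against.** The strongest reply is that the rule after the table already protects the decision. Progression requires a row to be in Green or Amber, not merely to avoid Red, so an uncoloured result fails that test. This stands. A reader might infer that a result which is not Red counts as a pass, and the text does not support that.

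A reader might also infer that the rule hides attrition bias. That does not hold either. Row d counts withdrawal from treatment. The Post-treatment and follow-up section keeps the follow-up assessment at its planned time for participants who discontinue. Data analysis includes all eligible randomised patients, and row e grades completion of the PDSS-A separately.

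Other parts of the plan could bring a failing arm to light. Recruitment and retention are reported by arm, and row b asks that no serious concerns be raised in questionnaires and interviews. These are useful, but they have no numerical limit for drop-out and do not give row d a colour. The wording also affects only these two rows; another row could still be Red.

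The size depends on the assumed rates. The one treatment drop-out result in the document is the adult brief-therapy trial in the Introduction, where nobody dropped out. If adolescents behave similarly, the gap seldom matters (1% at a true 5% in both arms).

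The condition could be read as each arm being graded separately. The text does not say so, and that reading would give two colours with no rule for combining them. The gaps between integer limits are minor, since such bands are naturally read as whole percentages.

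**Conclusion.** The point holds. As written, rows d and g give no colour to any result with the arms in different bands, and one failing arm cannot make the row Red. This conflicts with the stated intention of grading to one of three levels. The consequence is an undefined grade and a judgement made after the data are seen, not a false pass.

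The logical gap needs no assumption. Its frequency rests on independent binomial arms of 15 or 24 and on assumed true rates: about 1% when drop-out is very low, more than half once the true rate is 20 to 25% in both arms, and 90% or more at 10% versus 40%.

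This should be fixed, but it is not critical. The study is an unpowered single-centre feasibility trial, Red is worded as advisory, and an uncoloured row already fails the literal progression rule.

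**What to change.** Keep the sponsor's thresholds and let the worse arm decide, using contiguous limits on unrounded rates.

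- Row d: Green if drop-out is ≤ 20% in each arm; Red if it is > 30% in either arm; Amber otherwise.
- Row g: Green if sessions contain ≥ 80% allowable features in each arm; Red if < 70% in either arm; Amber otherwise.

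Every result then has exactly one colour. Only the wording of two table rows changes, and it should change before the criteria are graded.

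The cost is more Red by chance, which should be stated beside the rule. With 15 / 24 per arm it is 30% / 17% at a true 20% in both arms (2.7% / 0.8% now) and 53% / 41% at 25% (9.8% / 5.5% now). Because Red says only that a definitive trial may not be viable, such a result would prompt review and not an automatic stop.

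Other rules would also close the gap, such as separate arm grades with a stated combining rule, or a pooled rate. Pooling lets a good arm offset a bad one: 0/15 and 9/15 pool to 9/30 = 30%, which is Amber although one arm lost 60%.
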